#### 4. Analyses for specific aim 2.

**4.1 Mediation:** If the 3RP-NF intervention does show improvement in some or all of the primary and secondary outcomes among the sample in greater magnitude than the HEP-NF, we will explore the extent to which this relationship works through several possible mediators (some of the secondary outcomes: depression, anxiety, pain interference and pain intensity). To evaluate whether the intervention works in improving physical health QoL (as an example) through improved anxiety (as an example), we will conduct a product coefficients test for the effect of the intervention on anxiety as an intervening variable. For this test, we will estimate 2 regression models: the first will regress changes in anxiety on the intervention to determine the effect of the intervention on anxiety, and the second will regress changes in physical QoL on changes in anxiety while adjusting for treatment arm, to assess the effect of the intervention on physical health QoL while holding changes in anxiety constant. We will then calculate the product of coefficients,  $11$ , where  $11$  is the coefficient of the intervention as predictor of changes in physical health QoL in the first regression model, and  $1$  is the coefficient of changes in anxiety as a predictor of physical health QoL changes, controlling for intervention status, in the second regression model. Statistical significance of the mediated effect would be determined by the asymmetric distribution of product test, where lower and upper confidence limits will be calculated based on the product  $11$  and a critical value multiplied by the standard error of  $b$ . Evidence of mediation is supported if the confidence interval does not cover zero. The

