## II. SPECIFIC AIMS

The present proposal is based on qualitative formative work, an open pilot of the face-to-face 3RP-NF, and a pilot single blinded RCT of the 3RP-NF versus HEP-NF, both delivered via videoconferencing with Skype showing feasibility, acceptability, preliminary efficacy and durability. The objective of the study is to test, within a single blinded fully powered RCT, the efficacy of the 3RP-NF as compared to HEP-NF (attention control) in improving co-primary (physical and psychological quality of life) and secondary (social quality of life, environmental quality of life, depression, anxiety, pain intensity and pain interference) outcomes. **Specific aims:**

- Aim 1:** to determine the efficacy of 3RP-NF in comparison to an active control HLI on the co-primary outcomes: physical health QOL and psychological health QOL among patients with NF1, NF2 and schwannomatosis. Secondary outcomes are: social relationships QoL, environment QoL, depression, anxiety, pain, pain interference, gratitude, optimism, mindfulness, coping, social support, empathy and stress. Assessments will be conducted at baseline, post-intervention (8 weeks, primary time point), 6 and 12 months follow-ups (secondary time points). Both intervention and control are delivered via live video with Zoom.

**Hypotheses:** 3RP-NF will be more efficacious in reducing primary and secondary outcomes at post-intervention, and effects will be maintained at 6 and 12 months follow-ups, compared to HEP-NF.

- Aim 2:** to examine the degree to which treatment-dependent improvements in the primary outcomes are mediated by improvements in depression, anxiety, pain intensity, pain interference, gratitude, optimism, mindfulness, coping, social support, empathy and stress (conceptual mediators) and modified by NF type, age, race/ethnicity, learning disability and education level.

**Hypotheses:** Treatment-dependent improvements in the secondary outcomes depicted in the figure below will mediate benefits from 3RP-NR for the primary outcomes. The moderators NF type, age, and race/ethnicity will be associated with differential benefit from 3RP-NF for the primary outcomes.

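### Section VI.4.1 defines the first factor of the mediation product with a coefficient that its own first model does not contain, and it names 4 mediators where Aim 2 names 11

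*Protocol*

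**What the plan says.** Protocol section VI.4.1 (Mediation) describes a product-of-coefficients test, with physical health QoL and anxiety as the worked example.

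- First model: "the first will regress changes in anxiety on the intervention to determine the effect of the intervention on anxiety".
- Second model: "the second will regress changes in physical QoL on changes in anxiety while adjusting for treatment arm".
- First factor of the product: it "is the coefficient of the intervention as predictor of changes in physical health QoL in the first regression model".
- Second factor: it "is the coefficient of changes in anxiety as a predictor of physical health QoL changes, controlling for intervention status, in the second regression model".
- Decision rule: "Evidence of mediation is supported if the confidence interval does not cover zero".
- Effect size: the mediated effect as a share of the total effect.
- Condition for running the analysis: "If the 3RP-NF intervention does show improvement in some or all of the primary and secondary outcomes", in greater magnitude than the control.

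The same section gives the mediators as "some of the secondary outcomes: depression, anxiety, pain interference and pain intensity". Section II, Aim 2, speaks of primary-outcome improvements "mediated by improvements in depression, anxiety, pain intensity, pain interference, gratitude, optimism, mindfulness, coping, social support, empathy and stress". The assessment list in section V labels eleven instruments as both secondary outcome and mediator.

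**The concern.** The product of coefficients needs two paths: intervention to mediator (a), and mediator to outcome given arm (b). The sentence defining the first factor names intervention to outcome instead, and locates that coefficient in a model whose outcome is the mediator. It is the protocol's only definition of the Aim 2 test statistic.

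If the words were followed, the test would no longer ask whether treatment moved the mediator. It would ask whether treatment moved QoL and whether the candidate mediator correlates with QoL. The condition for running the analysis favours trials in which the first is true.

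This matters because an unmoved mediator is plausible here. The pilot trial (Study 5 in section I) found no greater improvement than control in depression or in pain intensity. It also says that a larger sample is needed for depression and pain interference. Three of the four mediators named in section VI.4.1 are therefore without an established treatment effect.

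The mediator list is a separate matter. Two sets of different size leave the extent of Aim 2 testing unfixed.

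**Working it through.** **1. The definitions side by side.**

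| Item | Outcome | Predictors | Intervention coefficient |
|---|---|---|---|
| First model | change in anxiety | intervention | a (intervention on anxiety) |
| Second model | change in physical QoL | change in anxiety, intervention | direct effect, given anxiety |
| First factor as defined | change in physical QoL | intervention | total effect c, said to come from the first model |

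The coefficient c is in neither model. The second factor is correctly defined as b.

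**2. What each reading gives.**

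- Correct: mediated effect = a × b; proportion mediated = (a × b) / c.
- Literal: mediated effect = c × b; ratio = (c × b) / c = b.

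The literal ratio is a slope in QoL units per mediator unit, not a proportion, and a does not enter it.

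**3. Illustration with pilot values.** Study 5 gives a = -2.32 (anxiety) and c = 7.69 (Physical Health QoL). The documents give no b, so a range is assumed.

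| Assumed b | a × b | (a × b) / 7.69 | c × b | (c × b) / 7.69 |
|---|---|---|---|---|
| -0.5 | 1.16 | +15% | -3.85 | -50% |
| -1 | 2.32 | +30% | -7.69 | -100% |
| -2 | 4.64 | +60% | -15.38 | -200% |

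For a symptom score, where lower is better, the literal reading also reverses the sign.

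**4. A mediator that treatment does not move (a = 0).** The protocol states no power or error rate for mediation, so there is no figure to reproduce. As a check on the inputs, take 106 per arm (half of the 212 expected at post-treatment), SD 14.7, difference 6.25 and two-sided 0.025:

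- 6.25 / (14.7 × √(2/106)) = 3.095; 3.095 - 2.241 = 0.854; power = 80.3%.

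The protocol states 80% for QoL Physical, so the inputs agree.

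A simulation with these inputs set a = 0. It used 2,000 trials per scenario and a 95% Monte Carlo interval for the product. The within-arm correlation between mediator change and QoL change is assumed, and so is the 95% level. The entries are the share of trials in which mediation is declared.

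| Total effect c | Correlation | Correct product | Literal product |
|---|---|---|---|
| 6.25 | 0.2 | 3.7% | 74% |
| 6.25 | 0.3 | 6.0% | 87% |
| 6.25 | 0.5 | 4.8% | 88% |
| 7.69 | 0.2 | 4.4% | 80% |
| 7.69 | 0.3 | 4.4% | 97% |
| 7.69 | 0.5 | 5.5% | 96% |

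The correct product stays near 5%. The literal product does not.

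**5. Mediator count.** Aim 2 lists depression, anxiety, pain intensity, pain interference, gratitude, optimism, mindfulness, coping, social support, empathy and stress: 11. The section V list also labels 11 instruments. Section VI.4.1 lists the first four only. With two QoL outcomes, and counting one visit, that is 11 × 2 = 22 tests or 4 × 2 = 8.

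**The case against.** The strongest reply is that nobody would carry out the wrong analysis. The two models are described correctly immediately beforehand. The faulty sentence itself points to the first model, and the only intervention coefficient there is a. The method is named as a product-of-coefficients test and is tied to the standard mediation literature. An analyst would have to disregard part of the sentence to arrive at c × b. This largely stands: the text contradicts itself rather than consistently prescribing a wrong test, and a is very probably what was meant. It does not remove the contradiction. Because the total effect is needed as the denominator of the proportion mediated, c will also be at hand.

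A reader might infer that the plan as a whole lets unmoved variables be declared mediators, or that the Aim 2 results will be wrong in size and sign. The documents do not support that. Those consequences follow only if the words of the one definition are taken over everything around them. The sizes shown also depend on assumed slopes and correlations.

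A reader might also fault the standard error used for the confidence limits. The symbols in that part of the section are damaged in the available text, so no claim is made about it.

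On the list, it can be said that section VI.4.1 sits under Aim 2, that all eleven scales are collected at every assessment, and that the section later extends the test to further mediators. That shows no data are missing. It does not settle which set applies, because the section restricts itself to some of the secondary outcomes and then names four.

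**Conclusion.** The point holds as an internal contradiction in a stated analysis rule. The first factor of the mediation product is defined by a coefficient absent from the model it cites, and the mediator set is 11 in two places and 4 in a third.

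The contradiction and the counts rest on the text alone. The illustrated harm rests on the literal reading. With b assumed between -0.5 and -2, the ratio is -50% to -200% where +15% to +60% is correct. With correlations of 0.2 to 0.5 and a 95% interval assumed, an unmoved mediator is declared in 74% to 97% of trials where about 4% to 6% is expected.

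Mediation is exploratory and conditional on observed benefit. The co-primary tests, the sample size and the primary efficacy conclusion are unaffected. The wording should still be corrected, since Aim 2 is one of the trial's two specific aims.

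**What to change.** 1. In section VI.4.1, in the definition of the first factor, replace physical health QoL by anxiety (in general, the mediator). The reference to the first regression model can stay. The definition of the second factor needs no change.
2. Choose one mediator list and state it identically in section II (Aim 2), the section V assessment list and section VI.4.1. Either add the seven missing mediators to section VI.4.1 or reduce the other two places to four. If the figure that the Aim 2 hypotheses refer to shows mediators, it should match.

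The cost is one phrase and one aligned list. No data collection, sample size or participant procedure needs to change if the eleven are kept, since all the scales are already scheduled.

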## MIND-BODY SKILLS TRAINING FOR ADULTS WITH NEUROFIBROMATOSIS

mediation effect size will be determined by the proportion of the total effect that is attributable to the mediation (i.e., the mediated effect divided by total effect). This test will also be conducted separately for the assessment of increases in the other mediators. The test will also be conducted separately for the psychological health QoL outcome. This method is consistent with Baron and Kenny (1986) and updated by Kraemer et al (2002); however, it extends the analysis by allowing us to test significance of the mediated effect, and quantify the magnitude of the mediation.

**4.2. Moderators:** The possible effect of moderators of a beneficial effect of 3RP-NF will be investigated by adding moderator (e.g., contrasting treatment response by NF1, NF2, and schwannomatosis diagnosis), moderator x treatment and moderator x treatment x visit interaction terms to the repeated-measures ANOVA described for Aim 1. Specific linear contrasts of the moderator x treatment x visit interaction terms will be used to test for differential 3RP-NF dependent benefit in improvements from baseline to post-treatment, 6 month, or 12 month follow-up that are a function of diagnosis, age, or race/ethnicity. Because in our previous work we showed that in a pooled sample of patients from the current RCT and our prior pilot (N=83) there were no significant differences in baseline scores on any outcome measures we are not powering the study to detect differences by NF type. Nevertheless, by stratifying randomization by diagnosis, we will optimize our power to detect differences by NF type given the available sample size and distribution of NF types.

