## V. STUDY PROCEDURES

Participants will be randomized 1:1 to 3RP-NF or HLI using a permuted-block randomization, stratified by diagnosis. Stratification ensures that an equal number of participants with NF1, NF2 and schwannomatosis are allocated to both treatments. Randomization will be generated by a computer.

We will use the same clinician/study therapist across the study conditions. Consideration was given to using different therapists for each arm to minimize potential contamination. However, observed study effects might be then attributable to clinician/therapist factors, and the study manuals are distinct. To deal with potential contamination, we will employ the audio-recording supervision and review as detailed below, including the use of checklists to document therapist fidelity to the intervention and also to prevent drift.

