## VI. BIOSTATISTIC ANALYSIS

**1. Missing data:** We will assess for patterns of missing data, which are expected to be low as the study uses computer-assisted questionnaire completion (REDCap), which reduces participant non-response (see how missing data is handled below). The primary anticipated reason for missing data is attrition due to loss of follow up. Based on our preliminary studies, in particular our videoconferencing RCT, we do not anticipate loss of data at time 2 (100% observed retention). However, we do anticipate some loss of data for the 6 (82.5% observed retention) and 12 months follow up. Conservatively, we estimate up to 5% loss to follow-up by post-treatment and up to 20% loss to follow-up by 12 months. Hence, we plan to enroll 224 participants to achieve at least 212 at post-treatment and 180 at 6 and 12 months. We will use mixed-model maximum-likelihood techniques for analysis to minimize bias when lost to follow-up is missing at random conditional on the observed data. Attrition effects will be evaluated by testing whether systematic differences exist between those participants who completed the research versus those who drop out. In this way we can determine the nature of the potential bias introduced by study attrition. If attrition is higher in the 3RP-NF group, multiple imputation and sensitivity analyses assuming a range of informative loss to follow-up will be investigated. Note that in our preliminary study, drop-out was more common in the placebo arm, which if it reflects lack of efficacy would yield conservative estimates of benefit from 3RP-NF.

**2. Evaluating possible confounders:** In the preliminary analyses we will examine the equivalence of the random assignment of groups with regard to key baseline characteristics. This will involve assessment of the treatment groups on sociodemographic characteristics, psychosocial variables and homework completion. In the unlikely event that important differences at baseline occurred by change even with randomization, we will run analyses both with and without these variables as covariates to determine whether baseline differences may account for differences in outcomes.

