post-intervention) and durability (to 6 and 12 months) of the 3RP-NF. Accordingly, the primary analysis will compare changes in primary and secondary outcomes (continuous measures) from baseline to the post-, 6 months and 12 months visits between the randomized conditions. All randomized participants will be included in our primary efficacy analyses as randomized, following the intention-to-treat principle. Data will be analyzed using a shared-baseline, linear mixed model with fully unstructured covariance among repeated measures. The shared-baseline assumption reflects the true state of the population prior to randomization and has the benefit of adjusting for chance differences at baseline. For each outcome, we will compare the effect of 3RP-NF vs. HEP-NF on changes from baseline to the post-test, 6 and 12 months follow-up times using linear contrasts. Our primary aim will focus on the post-treatment follow-up time. With two co-primary outcomes, we will use two-sided tests at  $p < 0.025$  to declare superiority of 3RP-NF, maintaining an overall 5% type 1 error at our primary post-intervention time point. Persistence of a benefit from 3RP-NF at 6 and 12 month follow-up times will be analyzed as a non-inferiority test of durability. Non-inferiority of 3RP-NF in maintaining benefits relative to HEP-NF will be declared if the lower one-sided 95% confidence bound for a given co-primary outcome is less than 6.25 units (the estimated MCID) in favor of HEP-NF. Several sensitivity analyses will be explored using alternative models. Change scores at post-intervention, 6 months, and 12 months will be separately analyzed by Wilcoxon rank sum test to avoid any parametric assumptions about the data. More parsimonious covariance structures will be considered using random participant-specific intercepts, slopes, and quadratic terms (i.e., growth curve analysis). Baseline parameters such as NRS pain will be included to account for chance differences due to randomization and to explain sources of variation in response that are independent of treatment group.

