While no information on clinically meaningful differences exists for the primary outcome measures for patients with NF, we will also use both “distribution-based” and “anchor-based” methods as criteria to determine important change. Consistent with “anchor based” methods, we will ask patients at post-treatment, 6 and 12 months follow ups to rate whether they were “substantially better”, “minimally better” “about the same”, “minimally worse” or “substantially worse” as compared to how they were before the intervention. These improvement ratings would thus serve as the standard with which to evaluate the importance to the patient of whatever changes in quality of life occurred during the intervention. Success of the trial will thus be estimated based on outcome score (quality of life scores) and anchor-based measures of subjective improvement. The anchor-based MCID estimates will be computed using prior methodology, as the mean change in the physical health and psychological health QoL among those in the “minimally better” category.

**3.1. Power Consideration and Sample Size Calculations.** The effective standard deviation (SD) for the change from baseline to post-treatment in QoL Physical and QoL Psychological based on a repeated-measures ANOVA of our preliminary data was 14.7 and 10.4 units, respectively. The effective SD from post-treatment to 6-month follow-up was 11.4 and 10.0 units, respectively. Based on these estimates, assuming an MCID of 6.25 units, allowing up to 5% loss to follow-up by post-treatment assessment, and testing each of the co-primary outcomes at  $p < 0.025$  two-sided, the study will have 80% power for QoL Physical and 96% power for QoL Psychological. Allowing up to 20% loss to follow-up by the 6-month assessment, the study will have 99% power to declaring non-inferiority of 3RP-NF vs. HEP-NF if the true treatment-dependent difference in maintenance of any change from baseline to post-treatment is zero.

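### The moderator model in VI.4.2 omits moderator x visit, so unless the contrast is fixed as a between-arm difference, a purely prognostic factor can pass as an effect modifier

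*Protocol*

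**What the plan says.** For Aim 1 (protocol VI.3): "Data will be analyzed using a shared-baseline, linear mixed model with fully unstructured covariance among repeated measures". Both arms share one baseline mean and may differ only after baseline. No moderator appears in that model.

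For Aim 2 (VI.4.2) the plan adds the moderator, "moderator x treatment and moderator x treatment x visit interaction terms to the repeated-measures ANOVA described for Aim 1". The test is then described: "Specific linear contrasts of the moderator x treatment x visit interaction terms will be used to test for differential 3RP-NF dependent benefit", applied to improvement from baseline to post-treatment, 6 months or 12 months as a function of diagnosis, age or race/ethnicity. Neither the coding of treatment nor the contrast weights are given. For diagnosis the section adds that "we are not powering the study to detect differences by NF type". Randomization is done "using a permuted-block randomization, stratified by diagnosis".

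**The concern.** Aim 2 asks whether the benefit of 3RP-NF over HEP-NF depends on the moderator. That is a difference between arms in how the moderator relates to change. To isolate it, the model must let the moderator relate to change in the control arm as well, which is the job of moderator x visit.

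Without that term, and with a 0/1 treatment indicator (3RP-NF = 1), the moderator effect in HEP-NF is forced to be the same at every visit. The three-way coefficient then describes how the moderator predicts change within 3RP-NF, not how the arms differ. If younger participants gained more from either programme, age could be reported as a moderator. A real moderator could also be hidden when the shared trend runs against it.

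There is a smaller second problem. A moderator x treatment term that acts at all visits lets the arms differ at baseline within moderator levels, which the shared-baseline model of VI.3 rules out.

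**Working it through.** **Inputs from the protocol**
- Planned numbers (VI.1): "we plan to enroll 224 participants to achieve at least 212 at post-treatment and 180 at 6 and 12 months". I use 212, so 106 per arm and 53 per arm-by-moderator cell for a 50/50 moderator.
- SD of change to post-treatment (VI.3.1): "based on a repeated-measures ANOVA of our preliminary data was 14.7 and 10.4 units, respectively". I use 14.7 (Physical). The SD of change from post-treatment to 6 months is 11.4.
- Effect size (VI.3.1): "assuming an MCID of 6.25 units".
- Baseline SD, Physical QoL (pilot Table 1): 17.76 and 21.16, so √((17.76² + 21.16²)/2) ≈ 19.5.

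**Assumptions not in the protocol:** two-sided 5% for moderator tests, complete data, a binary moderator, and a shared shift of 0, 3 or 6.25 units at all post-baseline visits.

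**Step 1. Check the inputs against the plan's own power.** SE = 14.7 × √(2/106) = 2.02. Power at two-sided 0.025 = Φ(6.25/2.02 − 2.24) = 80.3%. The plan states 80%.

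**Step 2. Implied correlations.** Baseline with later visits: 1 − 14.7²/(2 × 19.5²) = 0.716. Among later visits: 1 − 11.4²/(2 × 19.5²) = 0.829.

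**Step 3. What the three-way term estimates under 0/1 coding.** Write m for the moderator coefficient, mt for moderator x treatment, and mtv for the three-way term at visit v.

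| | Moderator effect at baseline | Moderator effect at visit v |
|---|---|---|
| HEP-NF | m | m |
| 3RP-NF | m + mt | m + mt + mtv |

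So mtv is the moderator's effect on change within 3RP-NF. The target is that quantity minus its HEP-NF counterpart, which this model fixes at zero.

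**Step 4. Size under 0/1 coding, with no effect modification.** Fitting the listed terms by generalised least squares with the Step 2 covariance gives, for the post-treatment three-way coefficient:

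| Shared shift | Expected estimate (truth 0) | SE | Rejection, Φ(est/SE − 1.96) plus lower tail |
|---|---|---|---|
| 0 | 0 | 2.80 | 5% |
| 3 | 2.86 | 2.80 | 17.5% |
| 6.25 | 5.96 | 2.80 | 57% |

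Simulation with an estimated unstructured covariance and all correlations at 0.716 (1,000 trials per setting) gives 56.3% at 6.25. With 29% in the smaller group, the pilot's share of non-NF1 patients, it gives 14.1% at 3.125 and 49.3% at 6.25. Adding moderator x visit brings rejection to 4–5% in every setting.

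**Step 5. Other ways to carry out the same sentence (shift 6.25, prevalence 50% / 29%).**

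| Implementation of the listed terms | False rejection |
|---|---|
| Class-coded treatment, explicit between-arm contrast | 5.2% / 5.2% |
| Effect-coded treatment (±0.5) | 4.7% / 4.9% |
| Class-coded, 3RP-NF coefficient alone | 62.7% / 52.8% |
| Class-coded, omnibus three-way test | 83.2% / 74.2% |

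**Step 6. Masking under 0/1 coding.** Suppose benefit truly differs by 6.25. With a shared trend of −3, the expected coefficient is 6.25 − 2.86 = 3.39 and power is Φ(3.39/2.80 − 1.96) ≈ 23%. With −6.25 it is 0.29 and power is about 5%. The corrected model has Φ(6.25/3.74 − 1.96) ≈ 39% in both cases (SE from Step 7).

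**Step 7. Cost of the all-visit moderator x treatment term.** Variance given baseline is 19.5² × (1 − 0.716²) ≈ 185.4; variance of change is 14.7² ≈ 216.1.
- Shared baseline kept in both moderator levels: SE = √(4 × 185.4/53) = 3.74.
- Baseline freed in one level by moderator x treatment: SE = √(2 × 185.4/53 + 2 × 216.1/53) = 3.89.

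**The case against.** The best reply is that the plan's wording points to a valid analysis. It speaks of a repeated-measures ANOVA and of linear contrasts across several interaction terms, which is the natural language of class-coded factors. VI.3 uses linear contrasts for a comparison of arms, and diagnosis and race/ethnicity are categorical. Under class coding the listed terms already span moderator x visit, and a between-arm contrast behaves exactly as in the full model. The omnibus test and the 3RP-NF coefficient alone are not what the section proposes. Coding and contrast weights are often left to a statistical analysis plan, which is not at hand.

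Most of this stands. A reader might infer that the planned test is invalid whenever a moderator is prognostic, or that prognostic factors will be reported as effect modifiers. The protocol does not support either reading, because it never commits to 0/1 coding.

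What remains is that the protocol does print a term list. An analyst who builds exactly those terms with a 0/1 indicator leaves moderator x visit out, and the sentence on contrasts does not say that they difference the arms. The coding reply also leaves the baseline point untouched, although moving the SE from 3.89 to 3.74 is a small matter.

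**Conclusion.** The point holds in conditional form. The listed terms omit moderator x visit, and whether the test of differential benefit keeps its nominal 5% depends on coding and contrast choices that VI.4.2 does not fix. Under 0/1 product terms and a 50/50 moderator, false rejection is about 17% for a shared shift of 3 units and 57% for 6.25. It is about 5% under a class-coded between-arm contrast. The protocol gives no information on how large a shared shift might be; 6.25 is a full MCID in both arms and sits at the high end of the range shown.

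This is a secondary analysis, not powered for NF type. A reader might extend the worry to the main efficacy result, but the co-primary comparisons contain no moderator terms and are unaffected.

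**What to change.** In VI.4.2, list the added terms as moderator, moderator x visit, and moderator x treatment x post-baseline visit. Drop the moderator x treatment term that acts at all visits, so that the shared baseline of VI.3 is kept. Define the test as the between-arm difference in change from baseline across moderator levels, at post-treatment, 6 and 12 months. The result then no longer depends on how the software codes treatment.

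Cost: a sentence or two of text and no new data. For each binary or continuous moderator, three parameters are added and one removed; NF type, with three levels, needs more. The SE at post-treatment is larger than in the 0/1 model as listed (about 3.7 against 2.8), but that smaller SE is valid only if the omitted term is truly zero. Against the class-coded version of the listed model, precision improves slightly.
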